## Abstract

**Highlights:**

**What are the main findings?**
Caregiving in Alzheimer’s disease is experienced as a continuum of relational, occupational, and identity-related losses that begins during active care and extends into bereavement.A convergent mixed-methods approach allows the integration of caregiver burden, health-related quality of life, and occupational balance with in-depth narratives of adaptation and meaning-making.

**What are the implications of the main findings?**
Publishing the protocol promotes transparency, reproducibility, and methodological transferability to other caregiving contexts and neurodegenerative conditions.The protocol facilitates the development and future evaluation of holistic, occupation-centered interventions adaptable across care settings and stages of the disease.

**Abstract:**

**Background**: Alzheimer’s disease (AD) is a progressive neurodegenerative disorder that severely affects cognitive, behavioral, and functional abilities, creating a substantial burden for family members who provide continuous care. Caregivers often experience role changes, occupational imbalance, emotional distress, and reduced quality of life, although some report personal growth. These experiences extend beyond active caregiving and include anticipatory grief during disease progression and grief after the relative’s death. Despite this continuum, few studies have examined caregiving, loss, and bereavement from an integrative perspective. This protocol describes a mixed-methods study aimed at exploring the lived experiences of family caregivers of individuals with AD, focusing on how evolving relational, occupational, and identity-related losses influence their well-being and adaptation. **Methods**: A parallel convergent mixed-methods design will be used. The quantitative component consists of a cross-sectional observational study including 66 caregivers recruited through purposive sampling across kinship categories (spouse/partner, adult child, grandchild) and care settings (home care with day-center attendance vs. institutionalized care). Data will be collected using the Zarit Burden Interview, Role Checklist, Short Form-36 Health Survey, and Occupational Balance Questionnaire. Descriptive and subgroup analyses will be conducted using SPSS (version 27). The qualitative component comprises a multiple-case study with approximately 36 participants across three groups: caregivers living with individuals with AD, caregivers of institutionalized relatives, and bereaved family members. Semi-structured interviews (45–80 min) will be conducted online or in person, transcribed verbatim, and analyzed thematically using MAXQDA (version 26). Integration will follow a concurrent approach, combining quantitative and qualitative results through joint narratives and displays to produce a comprehensive interpretation. **Discussion**: This study aims to deepen understanding of the caregiving–grief continuum in families affected by AD by integrating quantitative indicators of burden, health status, and occupational balance with qualitative accounts of adaptation and meaning-making. Findings are expected to support the development of holistic, evidence-based interventions that promote caregiver well-being throughout the care trajectory and during bereavement. **Ethics and Dissemination**: Ethical approval was granted by the Research Ethics Committee of Universidad Rey Juan Carlos (Code: 041220246522024; 15 October 2025). ClinicalTrials.gov Identifier: NCT07251738. Registered November 2025. Protocol version: Version 2.

## 1. Introduction

Alzheimer’s disease (AD) is defined as a progressive neurodegenerative disorder characterized by deficits in memory, language, and behavior [1]. It is a multifactorial disease of largely unknown etiology, with only a small proportion of cases having a clear genetic origin [2]. AD is the most common cause of dementia and leads to progressive neuronal damage in brain regions responsible for higher cognitive functions, affecting memory, thinking, language, and behavior [3].

According to the World Health Organization (WHO), more than 55 million people worldwide currently live with dementia, and this figure is expected to exceed 110 million by 2050. AD is also one of the leading causes of disability and dependence among older people, resulting in a gradual loss of autonomy and a significant impact on Activities of Daily Living (ADL), as well as on social and family relationships [4].

Given the limited effectiveness of pharmacological treatments, current care strategies increasingly focus on non-pharmacological interventions, such as cognitive stimulation, ADL training, and adapted physical activity, aimed at maintaining functionality and quality of life [5,6]. However, the progressive nature of the disease places a substantial burden on the family environment, where most care is provided.

In this study, the term caregiver refers to a family member who assumes primary responsibility for the care of a person with AD, providing ongoing physical, emotional, and social support, typically without financial compensation [7]. This role requires continuous adaptation and often entails a profound reorganization of daily life, including changes in routines, relationships, and personal priorities [8].

Previous research has shown that caregivers of people with AD are predominantly women, often spouses or daughters, who provide long-term, informal care [9,10]. This sustained commitment is associated with significant physical, psychological, and social consequences, including increased levels of caregiver burden, depressive symptoms, anxiety, sleep disturbances, and reduced quality of life [11,12]. In addition, caregiving frequently affects occupational balance, as caregivers struggle to maintain a satisfactory distribution of time and engagement across meaningful activities, including self-care, productivity, and leisure [13,14].

Nevertheless, caregiving is not exclusively associated with negative outcomes. Some caregivers report positive aspects, such as personal growth, strengthened emotional bonds, and the development of resilience and empathy [15]. However, as the disease progresses, caregivers often experience a series of cumulative and progressive losses, including changes in the identity and relationship with the person with AD, loss of shared roles, and disruption of future expectations.

In this context, increasing attention has been paid to the concept of anticipatory grief, understood as the emotional response to the expected loss that occurs before the death of a loved one. In dementia, this process may begin early in the disease trajectory and intensify as cognitive and functional decline progresses. Caregiving and bereavement are therefore not separate processes but form a continuum, in which caregivers experience ongoing losses before death and continue to process grief after bereavement [16,17,18].

Despite growing recognition of caregiver burden, fewer studies have explored this caregiving–bereavement continuum from a comprehensive perspective, integrating both the day-to-day caregiving experience and the grieving process before and after death. In particular, there is limited research examining how these experiences affect occupational balance, identity, and overall well-being.

Understanding caregiving as a dynamic and multidimensional process, from the assumption of the caregiving role to bereavement, is essential for designing effective support strategies. Given the complexity of this phenomenon, mixed-method approaches are particularly suitable, as they allow the integration of quantitative measures (e.g., burden, quality of life, occupational balance) with qualitative insights into caregivers’ lived experiences and meanings.

Therefore, this study protocol proposes a mixed-methods design aimed at comprehensively examining the life experience of caregivers of people with AD, with a particular focus on how cumulative losses (relational, occupational, and existential) influence their well-being, sense of identity, and adaptation. This protocol describes the theoretical and methodological frameworks, data collection procedures, recruitment strategies, integrated analysis plan, and ethical considerations. The findings are expected to contribute to the development of holistic support interventions that address caregivers’ needs throughout the caregiving and bereavement continuum.

### 1.1. Objective of the Study

The aim of this study is to comprehensively examine the impact of caring for a person with AD on caregivers’ daily lives using a mixed-methods approach by assessing caregiving burden, occupational roles, occupational balance, quality of life, and grief experiences.

The specific objectives are as follows:

#### 1.1.1. Quantitative Objectives

Objective 1: To analyse caregiving burden and changes in occupational roles among family members and/or caregivers of people with AD.

Objective 2: To assess the quality of life of family members and/or caregivers of people with AD.

Objective 3: To evaluate occupational balance among family members and/or caregivers of people with AD.

Objective 4: To compare caregiving burden, occupational roles, quality of life, and occupational balance between caregivers of people with AD who are institutionalized in nursing homes and those living at home.

#### 1.1.2. Qualitative Objectives

Objective 5: To explore caregivers’ lived experiences and perceptions regarding the impact of caring for a person with AD on their daily life and occupational participation.

Objective 6: To explore caregivers’ experiences of anticipatory grief and bereavement associated with the progression and loss of a person with AD.

#### 1.1.3. Mixed-Methods Integration Objectives

Objective 7: To integrate quantitative and qualitative findings in order to obtain a comprehensive understanding of how caregiving context and experiences shape caregivers’ occupational lives and well-being.

Although the quantitative component of this study is primarily exploratory, a set of a priori hypotheses is proposed to guide the analysis in line with the study objectives:

It is hypothesized that caregivers of people with AD living at home will report higher levels of caregiving burden, greater disruption in occupational roles, lower quality of life, and poorer occupational balance compared to those whose relatives are institutionalized (Objective 4).

In addition, it is expected that caregivers with closer family relationships (e.g., spouses) will present higher levels of emotional burden and greater alterations in occupational roles and balance compared to other family members (Objectives 1 and 3).

Finally, it is hypothesized that higher levels of caregiving burden will be associated with lower quality of life and poorer occupational balance (Objectives 1–3).

## 2. Materials and Methods

### 2.1. Study Design

For this project, a mixed-methods parallel convergent study will be designed. The purpose of mixed-methods research is to provide comprehensive and contextualized answers to questions raised in the health sciences, integrating different approaches to compensate for the limitations inherent in a single method or methodological perspective, through the parallel or simultaneous collection and analysis of qualitative and quantitative data [15].

A convergent design is particularly suitable for this study because the impact of caring for a person with AD involves both measurable outcomes and complex subjective experiences. Quantitative methods allow the assessment of caregiving burden, occupational balance, role performance, and quality of life, while qualitative approaches enable the exploration of caregivers’ lived experiences, perceptions of caregiving, and grief processes. The use of a convergent design will allow both types of data to be collected during the same phase of the study, analysed independently, and subsequently integrated to provide a more comprehensive understanding of caregivers’ experiences [15].

To this end, a quantitative observational cross-sectional study (QUAN) and a qualitative case study (QUAL) will be designed, with data collection and analysis for both methods carried out simultaneously. Qualitative case studies offer the opportunity to investigate in depth different perspectives of a specific health and disease phenomenon in its real context, using the perspective of people in their own social environment [19]. Cross-sectional studies, being observational in nature, offer a snapshot of the characteristics of subjects at a given point in time. However, they lack a follow-up period, which prevents the establishment of cause-and-effect relationships [20].

Integration of the quantitative and qualitative strands will take place during the interpretation phase of the study. Quantitative findings will provide measurable information about caregiving burden, occupational roles, occupational balance, and quality of life across caregiving contexts, while qualitative findings will offer deeper insights into caregivers’ experiences and the meaning attributed to caregiving and grief. The integration of both datasets will allow identification of areas of convergence, complementarity, or divergence between results, contributing to a more comprehensive understanding of how caregiving context and personal experiences shape caregivers’ occupational lives and well-being.

The development of this study protocol followed the SPIRIT 2025 guidelines [21]. Supplementary Material S1. The guidelines of the National Institutes of Health for mixed-methods research in health sciences [22] will be adopted for the development of this project. Likewise, the STROBE recommendations [23] will be followed for the observational study (QUAN), while the SRQR [24] and COREQ [25] guidelines will be followed for the qualitative design (QUAL).

The QUAN will focus on assessing occupational balance, role performance, caregiving overload, and quality of life among caregivers or family members of people with AD. To this end, two analysis groups will be established: one composed of people who live with family members with AD at home but attend a day center, and another composed of caregivers of family members institutionalized in a nursing home located in the Community of Madrid. Each group will be divided into three subgroups, depending on the family relationship to the person with AD (husband/wife, son/daughter, and grandson/granddaughter).

The QUAL will focus on exploring the experiences of family members/caregivers of people with AD with regard to caregiving and its impact on daily life. As in the QUAN design, two groups of participants will be established: family members who live with people with AD and family members who have institutionalized relatives with AD. In order to explore experiences in different family contexts and existing generational differences, these groups will be subdivided into three groups each to try to include different family roles (husband/wife, son/daughter, and grandson/granddaughter) in the study. In addition, a third group will be included to learn about the experiences of family members who have experienced the loss of a relative with AD.

Figure 1 illustrates the convergent parallel mixed-methods design used in this study. Quantitative and qualitative data will be collected during the same phase, analysed independently, and subsequently integrated during the interpretation stage.

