### 2.2. Sample/Participants

#### 2.2.1. Sampling Strategy and Number of Participants Included

For the development of this project, non-probabilistic purposive sampling will be used, based on the maximum variation technique [26,27]. This strategy allows participants to be deliberately selected to represent the greatest possible diversity within the phenomenon under study, with the aim of capturing different perspectives and experiences. In this case, variation will be ensured based on the different family roles played by caregivers and the institutionalization or home care status of the person with AD [26].

In qualitative studies, there is no formula for calculating sample size in advance, as there is no intention to extrapolate results or calculate statistical significance [27,28]. However, different authors consider multiple approaches and criteria to substantiate and determine sample size [29,30]. In the case of a multiple-case study, it is recommended to work with at least 2 to 4 cases to allow for comparison between them and enrich the analysis with different perspectives [31,32]. According to the authors, multiple case studies provide greater robustness to the analysis of the phenomenon than a single case study, as they allow different contexts and conditions to be explored, facilitating comparisons between them and increasing the credibility of the results obtained [31,32]. Therefore, for the present study, there will be a sample of 12 participants per group. Since there are three groups in the QUAL design, there will be a total of 36 participants.

In the QUAN design, the sample size was calculated using the G*Power program (version 3.1; one-factor ANOVA, three groups, 1:1:1 allocation) with a significance level (α) of 0.05 and a statistical power (1 − β) of 0.80. To detect a minimum difference of 12.62 units between groups, the result was 17 participants per group (n = 51). Considering a potential loss rate of 20%, the required recruitment size was adjusted to n = 51/(1 − 0.20) = 63.75. After rounding up and in order to maintain balanced groups, a total of 66 participants (22 per group) will be recruited. The sample size calculation was performed to ensure sufficient statistical power for group comparisons in the quantitative component of the study. Given the expected size of some subgroups, analyses involving subgroup comparisons will be interpreted with caution and considered exploratory.

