### 2.3. Recruitment

Participants will be recruited in a residential care home and a day care center. To this end, the principal investigator will hold meetings to explain what the project consists of, the different phases, and the various data collection tools. After this, those who express an interest in participating in the study will be contacted again to confirm their participation and sign the informed consent form.

For Group 3 (interviews with relatives who have lost a family member with AD), participants will be recruited through direct contact with a relative of a person with AD who has recently died and who was institutionalized in the residence where the sample will be recruited. Through this contact, an attempt will be made to recruit other family members who have suffered the loss of a person with AD. To this end, the principal investigator will hold meetings with participants who express their willingness to participate, in order to explain what the project consists of, the different phases, and the different data collection instruments. After this, those who express an interest in participating in the study will be contacted again to confirm their participation and sign the informed consent form.

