For the analysis of QUAN data, both descriptive and inferential statistical analyses will be performed. Descriptive statistics will be used to summarize the characteristics of the sample and the main study variables. The normality of the data will be assessed using histograms, normal Q-Q plots, and the Shapiro–Wilk test. Continuous variables will be described using mean and standard deviation or median and interquartile range, as appropriate, while categorical variables will be presented as frequencies and percentages. Inferential analyses will be conducted to explore potential differences between caregiving contexts (institutionalized care versus home care) and between family roles (husband/wife, son/daughter, grandson/granddaughter). Group comparisons will be performed using parametric tests (e.g., one-way ANOVA) or non-parametric alternatives (e.g., Kruskal–Wallis test), depending on data distribution and homogeneity of variance. Where appropriate, post hoc analyses will be conducted. Given the expected size of some subgroups, analyses involving subgroup comparisons will be interpreted with caution and considered exploratory. Statistical analyses will be performed using SPSS software (version 27).

The data will be integrated using a convergent parallel mixed-methods design, in which the QUAN and QUAL components will be collected and analyzed simultaneously [36]. Integration will take place during the interpretation phase by comparing and contrasting quantitative and qualitative findings to identify convergence, complementarity, or divergence between results. This process will enable the development of joint meta-inferences and a more comprehensive understanding of caregivers’ experiences. The results will be presented through integrated narratives and joint displays.

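### The quantitative strand can enrol several relatives of the same person with AD, but its sample size and tests assume independent participants; if relatives are co-enrolled and their scores correlate positively, the home-versus-institution p-values would be too small

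*Protocol article*

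**What the plan says.** The quantitative strand compares two settings, home care with day-center attendance and nursing-home care. Section 2.1 adds: "Each group will be divided into three subgroups, depending on the family relationship to the person with AD". The kinship levels are spouse, child and grandchild.

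Section 2.2.2 writes eligibility for relatives of people diagnosed with AD and sets no limit per person. The Introduction defines a caregiver as "a family member who assumes primary responsibility for the care of a person with AD", which would point to one participant per person with AD. However, neither the inclusion nor the exclusion criteria use that definition, and Section 2.1 describes the quantitative population as caregivers or family members.

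On recruitment, Section 2.3 states: "Participants will be recruited in a residential care home and a day care center". Section 2.2.1 describes purposive sampling that seeks variation in family role. It derives the sample size from a "one-factor ANOVA, three groups, 1:1:1 allocation", "with a significance level (α) of 0.05 and a statistical power (1 − β) of 0.80", and mentions no design effect.

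On analysis, Section 2.6 states: "Group comparisons will be performed using parametric tests (e.g., one-way ANOVA) or non-parametric alternatives", with Kruskal–Wallis as the example of the latter. The background variables listed in Section 2.4 include relationship and disease stage, but no code that links relatives of the same person.

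**The concern.** Relatives of one person with AD share that person's disease stage, care setting and care load, so their burden, quality-of-life and occupational-balance scores may well be correlated. One-way ANOVA and Kruskal–Wallis both assume independent observations. All relatives of one person also fall in the same setting. Positive correlation then adds between-family variance to the setting difference, and the tests do not count it.

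At stake is the error rate of the home-versus-institution comparison, which is Objective 4 and carries a directional hypothesis in Section 1.1.3. The kinship comparison is affected as well. If no family code is recorded at enrolment, the dataset may not allow a later correction.

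**Working it through.** **The plan's own figure.** Inputs from Section 2.2.1 are three groups, α = 0.05, power 0.80, a difference of 12.62 units, 17 per group (51 in total) and 20% loss.
- Loss step: 51/(1 − 0.20) = 63.75, rounded up to 64, then to 66 for three equal groups. This reproduces.
- The 17 per group can be neither confirmed nor refuted, because the article gives no SD and no Cohen's f. At N = 51 and power 0.80, the implied f is about 0.449. The implied SD is then 12.62 × √(1/6)/0.449 ≈ 11.5 if the middle mean lies at the centre, or 12.62 × (√2/3)/0.449 ≈ 13.3 if one group differs from two equal ones.
- Nothing in this calculation allows for family clustering.

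**Assumptions for the check.** The article gives neither the intraclass correlation (ICC) within families nor the number of relatives per family. ICC is taken as 0.1, 0.3 and 0.5. The layout is 66 participants, 33 per setting and 22 per kinship level, with no true difference. Each score is a shared family effect (variance ICC) plus an individual effect (variance 1 − ICC). Naive one-way ANOVAs at α = 0.05 were simulated 40,000 times per scenario.

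**Design effect for the setting contrast.** DEFF = 1 + (m − 1) × ICC, where m is the size-weighted mean family size.
- About half in pairs (8 pairs and 17 singles per setting): m = (8 × 4 + 17 × 1)/33 = 1.485. DEFF = 1.048, 1.145 and 1.242. Effective N = 66/DEFF = 63, 58 and 53.
- All in triads (11 per setting): m = 3. DEFF = 1.2, 1.6 and 2.0. Effective N = 55, 41 and 33.

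**Simulated type I error (nominal 0.05), for ICC 0.1 / 0.3 / 0.5.**

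| Who is enrolled | Setting test | Kinship test |
|---|---|---|
| One relative per person with AD | about 0.05 | about 0.05 |
| About half in mixed-kinship pairs | 0.055 / 0.068 / 0.078 | 0.048 / 0.039 / 0.034 |
| All in spouse-child-grandchild triads | 0.073 / 0.124 / 0.171 | 0.036 / 0.015 / 0.004 |
| Sibling pairs among children and among grandchildren, no cross-kinship links | 0.057 / 0.073 / 0.088 | 0.060 / 0.081 / 0.104 |

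**Cross-check.** Without clustering the critical value is 1.96. With it, the approximate type I error is 2 × [1 − Φ(1.96/√DEFF)]. For DEFF 1.145 this is 2 × [1 − Φ(1.83)] ≈ 0.067, and for DEFF 2.0 it is 2 × [1 − Φ(1.39)] ≈ 0.17. Both agree with the simulation.

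**Reading.** The setting test is anti-conservative in every clustered scenario examined. The kinship test is conservative when co-enrolled relatives differ in kinship, because the shared family effect then cancels from the contrast. It is anti-conservative when siblings share a subgroup.

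**The case against.** The strongest reply is that co-enrolment is nowhere stated. The Introduction's definition suggests one caregiver per person, and Section 2.2.3 excludes people who have neither lived with nor cared for the relative. With one relative per person there is no distortion. This stands, and it makes the point conditional. It does not remove it, because several relatives of one person can each meet the written criteria.

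The correlation is also assumed. The Zarit interview measures individual perceived burden, and if one member carries the care, others may carry less. A negative correlation would reverse the directions shown for the setting test. The documents do not settle this.

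The quantitative strand is called primarily exploratory, and subgroup comparisons are to be read with caution. That limits the consequence. The reason given for the caution is subgroup size, however, not dependence, and it does not clearly cover the two-group setting contrast.

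The tests are named as examples, and a fuller protocol or SAP may specify more. Model detail can be left there. Whether one or several relatives may enter is an eligibility rule, and the linking code has to be collected at enrolment.

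A reader might infer three stronger claims that the documents do not support:
- That the p-values are wrong as planned. This depends on who enrols.
- That kinship p-values would always be too large. Siblings within a subgroup push the other way.
- That the design fixes 22 spouses, 22 children and 22 grandchildren, or that Objective 4 is the main comparison. Section 2.2.1 says only 22 per group without naming the grouping factor, and no objective is ranked first.

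**Conclusion.** The point holds in conditional form. The sampling permits related participants and makes them likely, since grandchild and child cells must be filled from two facilities, while the sample size and the named tests treat everyone as independent. If relatives of one person enter and their scores correlate positively, the Objective 4 setting comparison rejects a true null too often. The excess is modest under partial pairing, close to nominal at ICC 0.1 and 0.078 at ICC 0.5. It is large only in the extreme all-triad case, where it reaches 0.17 at ICC 0.5. The kinship comparison would be invalid too, in a direction that cannot be fixed in advance. ICC and family structure are assumptions throughout. This is an inexpensive correction worth making before enrolment, not a flaw that undermines the study.

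**What to change.** State in Section 2.2.2 whether one or several relatives of the same person with AD may enter the quantitative strand.

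- **If several may enter:** add a coded identifier of the person with AD to the variables in Section 2.4, for every quantitative participant. If any person contributes more than one relative, replace the one-way tests in Section 2.6 with a linear mixed model that has setting and kinship as fixed effects and a random intercept for the person with AD. Use a small-sample degrees-of-freedom correction, because cluster-robust standard errors are unreliable with few families. If most families contribute one relative, the family variance will be poorly estimated, and the report should say so.
- **If only one may enter:** write that rule into Section 2.2.2. The named tests then need no change on this account.

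The first option costs one code per participant and one model term. The second makes grandchildren harder to recruit.
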